### Trial design and blinding

The trial is a stratified randomised controlled superiority trial with parallel arms using a 1:1 allocation ratio. It is stratified according to ‘active treatment’ and ‘post treatment’. The ‘active treatment’ group are those who are at least six weeks from their initial cancer diagnosis, and are currently undertaking major cancer treatments such as chemotherapy or radiotherapy. The ‘post treatment’ group are those who have completed their primary treatment for cancer [34] with no upper timeframe. Experimenters and Participants will be aware of their group allocation but as all measures are self-report blinded assessors will not be required.

### Randomisation

Accepted participants will be stratified according to their phase in their cancer experience into the ‘active treatment’ group and ‘post-treatment’ group as described earlier. Thereafter, they will be randomised based on an allocation sequence generated by an independent person not involved in the study via a true randomisation process (www.random.org). Numbers corresponding to treatment group (1 = iCBT) or the treatment as usual group (2 = TAU) will be placed in sealed opaque envelopes bearing the sequential order number to ensure participant allocation based on the pre-determined randomisation sequence. A member of the research team will open the envelope after the diagnostic interview.

### Trial procedure

Figure 1: Participant Flow Chart details the time line for participants in the study. Once randomised, participants will be allocated to either the iCBT arm or the TAU arm. Over the sixteen week period, both groups undertake the same set of measures three times, the start, mid-point and end of the intervention. In the iCBT group, these times will vary according to when the participant undertakes the specific lesson; whereas for the TAU group, the questionnaires are according to specific times (i.e. weeks since commencement of group). Administration time points for measures are contained in Table 1. Baseline records of psychotropic medications and whether they are accessing psychological support will be captured for participants in both groups. Participants will be asked to inform the research team if any of their current interventions change.

**Table 1 Tab1:** Administration time points for questionnaires used in the RCT

Measure	Pre-treatment^a^	Before each lesson^b^	Mid –treatment^c^	Post-treatment^d^	3-month follow-up^b^
HADS-T	♦		♦	♦	♦
K-10	♦	♦	♦	♦	♦
PHQ9-Q9	♦		♦	♦	♦
BDI-II Item 9	♦		♦	♦	♦
FCRI	♦		♦	♦	♦
FACT-G	♦		♦	♦	♦
CEQ	♦			♦	
ADIS	♦				♦

*HADS-T* Hospital Anxiety and Depression Scale,Total score, *K-10* Kessler-10 Psychological Distress Scale, *PHQ9-Q9* Patient Health Questionnaire 9-itme scale, Question 9, *BDI-II Item 9* Beck Depression Inventory-II, Item 9, *FCRI* Fear of Cancer Recurrence Inventory, *FACT-G* Functional Assessment of Cancer Therapy – General, *CEQ* Credibility and Expectancy/Satisfaction Questionnaire, *ADIS* Anxiety Disorders Interview Schedule for DSM-5

^a^iCBT group pre Lesson 1; TAU group at week 1 (Baseline)

^b^iCBT group only

^c^iCBT group pre Lesson 5; TAU group at week 8

^d^ iCBT group post Lesson 8; TAU group at week 16 (End)

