### Measures

#### Primary outcome measure

### Hospital anxiety and depression scale, total score (HADS-T)

The primary endpoint is anxiety and depression severity at post treatment as measured by the Hospital Anxiety and Depression Scale Total score (HADS-T) [35]. The HADS was developed as an outcome measure to assess anxiety and depression that avoids reliance on the measurement of somatic symptoms (e.g., fatigue, or insomnia) that may be experienced by people with cancer as part of the presenting illness. HADS-T is a fourteen item self-report questionnaire divided into two sub-scales, HADS-D, depression subscale and HADS-A, an anxiety subscale. The HADS-T is the total HADS score and is the combined score of the depressive and anxiety sub-scales. High scores indicate greater morbidity. This validated measure is widely used in clinical settings and has been validated in cancer patients [29].

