### Statistical methods

There is no prior published research outlining effectiveness of iCBT for treatment of a clinical depression or anxiety disorder in a cancer setting. In order to calculate sample size, data was taken from published randomised controlled trial of a transdiagnostic iCBT program [26]. Assuming the effect size of >0.6, and taking power at 80% with alpha set at 0.05%, sample size is calculated to be 44 per group. This is to detect a 0.6 effect size for the iCBT group to improve more than the treatment as usual group. Recruitment of 50 per group will be undertaken to account for attrition.

All analyses will be conducted at conclusion of the trial period, i.e. when all participants in the treatment group have completed the iCBT program. All analyses will be implemented in SPSS. Consideration will be given to the stratification into ‘active treatment’ and ‘post-treatment’.

Significance testing of group differences regarding demographic data and pre-treatment measurements will be conducted using analysis of variance (ANOVA) and *χ*2 where the variables consist of nominal (or categorical) data. Intent-to-treat (ITT) mixed models using restricted maximum likelihood (REML) estimation will be used to account for missing data due to participant drop-out. Mixed models do not assume that the last measurement is stable (the last observation carried forward assumption) [48, 49]. REML models are appropriate for RCTs with multiple time points and pre-to post-only designs [50]. The assumption that data are missing at random (MAR) will be evaluated using binary logistic regression to predict drop-out (0 = no drop-out, 1 = drop-out) and by comparing these two groups on baseline measures. Significant effects will be followed up with pairwise contrasts comparing mean pre-treatment to mean post-treatment scores. Mediation analyses will be used to examine the association between change in depression and anxiety symptoms over treatment and change in each of FCRI and FACT-G in separate analyses. Tests of the indirect effects (mediation) will be conducted using PROCESS [51].

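### The primary HADS-T is scheduled by lesson progress in iCBT but by calendar week in TAU, and no week-16 assessment is described for iCBT participants who stop early

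*Protocol article*

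**What the plan says.** The Measures section states: "The primary endpoint is anxiety and depression severity at post treatment", using the HADS total score. Table 1 (Trial procedure) defines post-treatment separately by arm: "iCBT group post Lesson 8; TAU group at week 16 (End"). The mid-point is defined the same way: "iCBT group pre Lesson 5; TAU group at week 8". The text above the table confirms that this is intended: "In the iCBT group, these times will vary according to when the participant undertakes the specific lesson", with TAU timed in weeks since the group began. The same section sets a common frame: "Over the sixteen week period, both groups undertake the same set of measures three times, the start, mid-point and end of the intervention".

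Study design allows for fewer than eight lessons being taken. Statistical methods plans an intention-to-treat mixed model fitted by REML to deal with drop-out. It examines the missing-at-random assumption with a logistic regression for drop-out and a comparison of drop-outs and others on baseline measures. Analysis is to start at the end of the trial period, explained as "i.e. when all participants in the treatment group have completed the iCBT program".

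**The concern.** The event that prompts the primary measurement is part of the treatment process in one arm and a date in the other. This has two consequences.

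- **Missing data.** Under the schedule as written, whether an iCBT participant has a post-treatment HADS-T depends on finishing the program. TAU has no such condition. If people who stop early benefit less, their absence raises the estimated effect.
- **Timing.** An iCBT participant who finishes quickly is measured before week 16 and compared with controls measured at week 16. Any natural change over the remaining weeks is then mixed with the treatment effect.

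This is a rule for collecting data, and a later analysis plan cannot recover scores that were not requested. What is at stake is whether the primary estimate is an intention-to-treat effect or something closer to the effect in completers.

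**Working it through.** **Inputs from the documents.** The planned effect is 0.6 SD, with 80% power and 50 recruited per group (Statistical methods). The alpha is read as 0.05, as in the Abstract. No Lesson 8 completion rate, non-completer effect or distribution of assessment times is given, so these are assumed below.

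**1. The plan's own figure.** n per group = 2(1.96 + 0.84)² / 0.6² ≈ 43.6, so 44, as Statistical methods states. The t-test version gives 44.6, so 45, as in the Abstract. The 0.6 used below is therefore the plan's own target.

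**2. Effect if everyone were measured.** Let m be the share of iCBT not finishing Lesson 8, and e their benefit over TAU. The intention-to-treat effect is (1 − m) × 0.6 + m × e.

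| m | e | True effect | 0.6 ÷ true effect |
|---|---|---|---|
| 20% | 0 | 0.80 × 0.6 = 0.48 | 1.25 |
| 40% | 0 | 0.60 × 0.6 = 0.36 | 1.67 |
| 20% | 0.3 | 0.48 + 0.06 = 0.54 | 1.11 |
| 40% | 0.3 | 0.36 + 0.12 = 0.48 | 1.25 |

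The last column applies if the model estimate equals the completer effect, which is the upper end.

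**3. How much the pre-Lesson 5 score helps.** Non-completers stay in the model through their baseline score and, if they reached Lesson 5, their mid-point score. Assume a correlation of 0.6 between any two time points and half of each benefit present by the mid-point. The slope of the post score on the mid score, given baseline, is 0.6 / (1 + 0.6) = 0.375. With e = 0, non-completers lie 0.3 SD behind completers at mid-point. If all of them gave that score, the estimate is 0.6 − 0.375 × m × 0.3:
- m = 20%: 0.6 − 0.0225 = 0.578, against a true 0.48
- m = 40%: 0.6 − 0.045 = 0.555, against a true 0.36

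If none reached Lesson 5, the estimate stays at 0.60 in both cases. Under these assumptions the mid-point score removes only a small part of the bias.

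**4. Timing.** Assume TAU improves naturally and linearly by d SD over 16 weeks. Measuring an iCBT participant at week t rather than week 16 shifts the contrast against iCBT by d × (16 − t) / 16. For d = 0.1–0.3, the shift is 0.025–0.075 SD at week 12 and 0.05–0.15 SD at week 8. If TAU worsens over time, or if iCBT assessments fall after week 16, the sign reverses.

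**5. Power.** With d = 0.6 and TAU fully observed, power is about 80% for 40 versus 50 observed and 77% for 35 versus 50. Loss of numbers is a minor matter beside bias.

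**The case against.** The strongest reply has four parts.

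- **The article does not say that non-completers go unassessed.** A reader might infer that they are never asked and so have no primary outcome. That goes further than the text. Both arms are placed in a sixteen-week period, clinicians follow up unexplained breaks from logging in, and the flow chart, which is not shown, could carry a calendar rule. What stands is that Table 1 and the text define the iCBT assessment by lesson and describe no fallback.
- **The mixed model uses all available scores.** This is true of baseline and any pre-Lesson 5 score. Table 1 also schedules a 3-month HADS-T for iCBT without tying it to Lesson 8. However, the article does not say whether that score enters the primary model, and TAU has no counterpart. The missing-at-random check relates drop-out to observed measures only, so it cannot exclude dependence on the unseen outcome.
- **Timing may work against iCBT.** This is correct where controls improve naturally and iCBT participants finish early. It is not a safeguard, because neither direction nor size is controlled.
- **The analysis trigger is loose wording.** A reader might infer that it can never be met, since some participants will not finish. The reference to the end of the trial period makes a milder reading more natural: that the last program period has ended.

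A reader might also infer that acceptability will be overstated, because the satisfaction items are given post-treatment. Those items ask about skills the program taught, so asking afterwards is natural. Bias there is possible but not shown.

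**Conclusion.** The point holds as a design fault. The primary assessment is lesson-triggered in iCBT and calendar-triggered in TAU, with no stated calendar-based HADS-T for iCBT participants who do not reach Lesson 8. Following the text ties missing primary outcomes to non-adherence in one arm and compares the arms at different elapsed times. The planned model removes the missing-data bias only under an assumption that the planned check cannot establish.

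The bias favours iCBT if non-completers benefit less; the timing effect may go either way. The size is unknown. The contrast of 0.48–0.36 with an estimate approaching 0.6 rests wholly on an assumed 20–40% non-completion and no benefit in non-completers. With half the benefit in non-completers, the true effect would be 0.54–0.48. The documents support neither set of values over the other. They also do not support a claim that the trial is underpowered for this reason.

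**What to change.** - Send the HADS-T and the secondary battery online to every participant in both arms at weeks 8 and 16 from randomisation, whatever lessons have been done.
- Define the primary endpoint as HADS-T at week 16 from randomisation.
- Keep the lesson-triggered scores for monitoring.
- Reword the analysis trigger: the primary analysis starts when the last participant in either arm has passed the week-16 assessment.

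**Cost.** The change needs a protocol amendment and reprogramming of the Virtual Clinic software, which already sends TAU its week 8 and week 16 questionnaires. Some iCBT participants answer an extra set. The estimate may be smaller: under the no-benefit illustration, power with 50 per arm is about 66% at an effect of 0.48 and 43% at 0.36. Enrolment began in March 2016, so participants already past week 16 may have only lesson-triggered scores. Their data should be analysed by actual assessment date, and the report should say how many are affected.

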### Description of the interventions

#### Internet delivered CBT (iCBT), the ‘iCanADAPT Early’ program group

The ‘iCanADAPT Early’ Program is a self-managed, 16 week online cognitive-behavioural intervention consisting of eight lessons involving general CBT skills and then cancer-specific CBT skills. Content is presented in the form of an illustrated comic-based storyboard in which two animated characters gain mastery over their anxiety and depressive symptoms with the help of a clinician. The female character is currently undergoing cancer treatment and tackling clinical levels of depression, while the male character is post-treatment with predominant anxiety symptoms. The participant follows both characters journeys to recovery across the 8 lessons. The *title*, and expansion of the main focus of each lesson are in Table 2: Course overview.

**Table 2 Tab2:** Course overview

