### Secondary outcome measures

**Kessler-10 Psychological Distress Scale** (K10) [36]: The K10 contains 10 items ranked on a 5-point scale designed to measure non-specific psychological distress. High scores indicate higher distress. The K10 has been validated in a mixed cancer-type population [37]. Furthermore, the K10 is a quickly administered online tool and is advantageous for monitoring iCBT patients [38]. For the current study, the time frame was modified to assess psychological distress in the past 2 weeks rather than the past 30 days.

**Patient Health Questionnaire 9-item scale, Question 9** (PHQ9-Q9 [39]) **and Beck Depression Inventory-II, Item 9** (BDI-II,i9), [40]: The HADS-T and the K-10 do not contain questions regarding either a passive death wish or suicidal ideation. Therefore, these two screening questions for ‘better off dead’ thoughts and suicidality are included in the assessment of patients, and score changes are automatically reported. These questions allow the monitoring clinician to make contact with participants should changes occur.

**Fear of Cancer Recurrence Inventory** (FCRI) [41]: The 42-item Fear of Cancer Recurrence Inventory was chosen as it is an aggregate score of seven sub-scales ranging from triggers to level of insight into the problem. The FCRI severity subscale is reported to be the most informative regarding a patient’s level of fear [42]. High scores indicate greater fear of cancer recurrence. Possible associations between the FCRI subscale scores and the clinical diagnoses via the ADIS, and/or other determinants [43] including treatment response, will be assessed.

**Functional Assessment of Cancer Therapy – General** (FACT-G, version 4) [44]: The FACT-G is a 33-item general cancer quality-of-life measure. FACT-G has been established as a valid and reliable measure [45]. FACT-G was chosen over other quality of life measures as it has scales looking at the impact of symptoms on relationships and supports [46].

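### In the iCBT arm the two suicidality items are repeated only when Lesson 5 is reached and Lesson 8 is finished, so a participant who stalls early is sent neither item again during the program

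*Protocol article*

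**What the plan says.** The Trial procedure section of the protocol article sets out the intent for both arms: "Over the sixteen week period, both groups undertake the same set of measures three times, the start, mid-point and end of the intervention". It then separates the arms. For iCBT, "In the iCBT group, these times will vary according to when the participant undertakes the specific lesson"; by contrast, "for the TAU group, the questionnaires are according to specific times", counted in weeks.

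Table 1 marks PHQ9-Q9 and BDI-II item 9 at pre-, mid- and post-treatment and at 3-month follow-up (iCBT only). It has no mark for them in the column for measures given before each lesson; only the K-10 has one. Footnote c defines the mid-treatment point as "iCBT group pre Lesson 5; TAU group at week 8". Footnote d sets the post-treatment point after Lesson 8 for iCBT and at week 16 for TAU.

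The Secondary outcome measures section explains why the two items are there: "The HADS-T and the K-10 do not contain questions regarding either a passive death wish or suicidal ideation". It adds that changes in these scores are reported automatically so that a clinician can get in touch.

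The intervention is described as a self-managed "16 week online cognitive-behavioural intervention consisting of eight lessons". On the time line, the article refers the reader to a figure that is not reproduced in the text at hand: "Figure 1: Participant Flow Chart details the time line for participants in the study".

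**The concern.** The two items are a safety measure. They were added because the other distress scales ask about neither topic, and they work by comparing a new score with an older one. In the iCBT arm a new score depends on progress through the lessons. A participant who stops progressing is also the one for whom the next score is never triggered. The K-10 given before lessons does not fill the gap: it stops when the lessons stop, and it has no question on the subject.

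Everyone in the trial has a diagnosed depressive, anxiety or adjustment disorder, the program is self-managed, and the Statistical methods section plans for attrition. A stall before Lesson 5 is therefore foreseeable. At stake is whether worsening suicidality during the program would be picked up by the scheduled items. The estimated treatment effect is not at stake here, because no planned analysis uses these two items as an outcome.

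**Working it through.** This is a count of scheduled administrations. Power and alpha play no part.

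**Inputs**
- Intended administrations in 16 weeks, both arms: 3 (Trial procedure).
- iCBT time points: before Lesson 1, before Lesson 5, after Lesson 8 (Table 1, footnotes a, c, d).
- TAU time points: weeks 1, 8 and 16 (same footnotes).
- Program: 8 lessons in 16 weeks (Description of the interventions).

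**The plan's own figure.** An iCBT participant who finishes has 3 scheduled scores, and a TAU participant has 3. This reproduces the stated three.

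**Scheduled in-program scores by progress, iCBT**
- Finishes Lesson 8: 3.
- Starts Lesson 5 but does not finish Lesson 8: 2.
- Stalls before Lesson 5: 1, so 3 − 1 = 2 of the 3 intended scores are never triggered.

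**Intervals without a scheduled item**
- Planned pace: 16 weeks / 8 lessons = 2 weeks per lesson. From the start of Lesson 1 to the start of Lesson 5 is 4 × 2 = 8 weeks; from the start of Lesson 5 to the end of Lesson 8 is again 4 × 2 = 8 weeks.
- TAU: 8 − 1 = 7 weeks, then 16 − 8 = 8 weeks.
- iCBT, stalled before Lesson 5: up to 16 weeks from baseline to the end of the program; 16 / 8 = 2 times the planned-pace interval.

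At the planned pace the arms hardly differ. The gap arises only for those who stall. Their next scheduled item is at the 3-month follow-up, outside the 16 weeks. I put no length on that further wait, because the article does not say from which date follow-up is counted for someone who never finishes.

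**After the change proposed below.** With week-8 and week-16 defaults, every iCBT participant has 3 scheduled scores, whatever lesson is reached.

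**The case against.** The strongest objection is that a stalled participant is not left alone. The section on clinician guidance for the iCBT group has each participant's scores and activity watched through the working week. It sets individual email contact after Lessons 1 and 2 as a minimum, and names stopping logging in without explanation among the typical reasons for further email or phone contact. At entry, a BDI-II item 9 score of 2 or more excludes the applicant, a psychiatry doctor conducts the interview where there is any concern about risk, and general practitioner details are required. This all stands and lowers the weight of the point. It does not remove it: the minimum contacts are themselves tied to lessons, no interval is given for contact after a break, and the text does not say that either item is asked then. The entry checks describe the participant's state at entry, not later change.

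A second objection is that a calendar default may exist in Figure 1 or in the full protocol, neither of which is at hand. That is possible, and the fix is worded accordingly. The point does not rest on silence alone, however: the article states the lesson-based rule outright.

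Four stronger readings are tempting, and the document supports none of them.
- A reader might infer that the automatic report has nothing to compare for an early staller. Suicidality scores are already used at or before the entry interview, so a comparison of entry with pre-Lesson 1 may be possible. Both scores precede the program; only change during it is missed.
- A reader might infer that TAU participants are assured three scores. The count is of scores scheduled. A TAU participant who ignores weeks 8 and 16 also yields one, and the TAU guidance section names no contact for non-response.
- A reader might infer that iCBT participants are less well watched overall. In clinician contact they are better covered: TAU participants get a generic email, and a clinician makes contact only for unexpectedly high or markedly changed scores.
- A reader might infer that the protocol contradicts itself. The three administrations are the nominal schedule, and the article openly says that the iCBT times vary.

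**Conclusion.** The point holds as a minor safety improvement. Under the stated rule, an iCBT participant who stalls before Lesson 5 is sent neither item again after the pre-Lesson 1 score until the 3-month follow-up. That is 1 of 3 intended in-program scores, and up to 16 weeks without a scheduled item instead of 8. One who stops between starting Lesson 5 and finishing Lesson 8 has 2 of 3. For these participants, detection during the uncovered period rests on clinician contact.

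This assumes that the footnotes to Table 1 are the operating rule and that neither Figure 1 nor the full protocol adds a calendar default. The article does not say how many participants would stall, and no number is assumed here. The conclusion does not extend to any claim of harm or of bias in a planned analysis.

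**What to change.** Add a calendar default under Table 1: PHQ9-Q9 and BDI-II item 9 go at week 8 to any iCBT participant who has not reached Lesson 5, and at week 16 to any who has not finished Lesson 8. If Figure 1 or the full protocol already provides this, a sentence under Table 1 saying so is enough. Optionally, clinicians could ask the two items when they make contact after a break, since someone who has stalled may also ignore an automated prompt. How clinicians respond to a score remains for the sponsor to decide.

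The cost is at most 2 prompts × 2 items = 4 answers per stalled participant, on a system that already times the TAU questionnaires by week. The downsides are slight participant burden, a few extra alerts for clinicians and some unanswered prompts.

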**Methods/design:**

Early stage cancer survivors will be recruited via the research arm of a not-for-profit clinical research unit and randomised to an intervention (iCBT) group or a ‘treatment as usual’ (TAU) control group. The minimum sample size for each group is 45 people (assuming effect size > 0.6, power of 80%, and alpha at .05), but 10% more will be recruited to account for attrition. A solitary or cumulative diagnosis(es) of Major Depressive Episode (current), Generalised Anxiety Disorder, Illness Anxiety Disorder, Panic Disorder, Agoraphobia, and/or Adjustment disorder will be determined using modules from the Anxiety Disorders Interview Schedule for DSM-5. Depression and anxiety levels with be measured via the total score of the Hospital Anxiety and Depression scale (HADS-T), the primary outcome measure. Secondary measures will include the Kessler 10 to measure general distress, the Fear of Cancer Recurrence Inventory (FCRI) to measure the specific fear of cancer recurrence and the Functional Assessment of Cancer Therapy, General Version 4 (FACT-G) for self-report of physical, social, emotional and functional well-being. iCBT participants will complete the measures before lessons 1 and 5, at post-treatment and at 3-month follow-up. The TAU group will complete similar measures at weeks 1, 8 and 16 of the waiting period. Program efficacy will be determined using intent-to-treat mixed models. Maintenance of gains will be assessed at 3-month follow-up. Mediation analyses using PROCESS will be used to examine the association between change in depressive and anxious symptoms over time and changes in FCRI and FACT-G QOL in separate analysis.

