## Hypotheses

The hypotheses are that, in a patient population characterised by comorbid early stage cancer survivorship AND a clinical depression and/or anxiety disorder:iCBT plus treatment as usual will produce clinically relevant decreases in depressive and anxious symptoms as shown by a decrease in the total Hospital and Anxiety Depression Scale (HADS-T) score (primary outcome measure) compared to a control group receiving treatment as usual.iCBT plus treatment as usual will produce clinically relevant decreases in general distress (Kessler 10), fear of cancer recurrence (Fear of Cancer Recurrence Inventory (FCRI)) and physical, social, emotional and functional status (as measured by the Functional Assessment of Cancer Therapy-General Version scale (FACT-G QOL)).iCBT plus treatment as usual will be perceived by patients to be credible (Credibility/Expectancy Questionnaire(CEQ)), and to be likely to produce positive impacts.

The RCT was approved by the St. Vincent’s Hospital National Human Research Ethics Committees (reference: HREC/15/SVH/432).

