## Clinician guidance for iCBT group

Each participant’s scores and engagement are monitored over the course of the working week. At minimum, individual email contact is made to each participant after the completion of Lesson 1 and Lesson 2. Thereafter, further email and/or phone contact will be made to participants depending on their needs. Typical reasons for clinician contact include an increase in distress scores, a participant question relating to content or a participant taking an unexplained break from logging in. Participants will have the opportunity to volunteer feedback about their most recent lesson/week(s) before each subsequent lesson and these responses will occasionally prompt clinician contact.

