### Treatment as usual (TAU) group

Participants allocated to the TAU group may access their local general practitioner, community or cancer centre (mental) health services during the course of their waiting period.

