## Clinician guidance for TAU group

Each participant’s questionnaire responses (week 1, 8 and 16) are reviewed. A generic email is sent from the Virtual Clinic system to thank participants for completing their questionnaire. Clinician contact will only be made if there are unexpected high HADS, or K-10 scores, or significant change from the scores previously obtained. Upon completion of the 16-week waiting period, and upon completion of the final set of TAU questions, the participants will transition to iCBT and then receive clinician guidance during their iCBT program as described above.

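### After baseline, outside care is known only if participants report it, and controls waiting for iCBT have a reason not to, so the trial cannot reliably describe the usual care each arm received

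*Protocol article*

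**What the plan says.** The Hypotheses section sets iCBT plus treatment as usual against no iCBT, "compared to a control group receiving treatment as usual". The Abstract describes the same control period as a wait: "The TAU group will complete similar measures at weeks 1, 8 and 16 of the waiting period". The section on the TAU group lets controls use their general practitioner and "community or cancer centre (mental) health services during the course of their waiting period". The section on clinician guidance for the TAU group says what happens once the wait is over and the last questionnaire is in: "the participants will transition to iCBT and then receive clinician guidance during their iCBT program as described above".

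The Trial procedure section covers the recording of other care. At the start, "Baseline records of psychotropic medications and whether they are accessing psychological support will be captured for participants in both groups". After that, "Participants will be asked to inform the research team if any of their current interventions change". Table 1 lists the questionnaires by time point and has no item on care received.

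The consent paragraph that closes the section on inclusion and exclusion criteria adds a rule for one arm. Participants randomised to TAU are told that if they begin a CBT intervention or a new psychotropic outside the trial, their data will be omitted. No matching rule is stated for the iCBT arm. The Statistical methods section calls the analysis intent-to-treat.

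**The concern.** A comparison with usual care can be interpreted only if the reader knows what that care was. Here the comparator is usual care received by people waiting for the trial treatment, and its content after baseline depends on participants coming forward. Controls are told of a consequence, loss of their data, that follows from two kinds of new care. A control who wants to stay in the study therefore has a reason not to mention them, and iCBT participants are given no such reason.

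The protocol's own rule also relies on this information. Omission can be applied only to those controls whose new care becomes known, so who is removed would depend on who reports.

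The stake is interpretation. The Discussion says that, if efficacious and acceptable, the program would join the treatments offered to cancer survivors and would be a core component of a further cluster-randomised trial. Readers of the result will want to know what iCBT was added to and what it was compared with.

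**Working it through.** **The plan's own figure.** Inputs from Statistical methods: standardised effect 0.6 and power 80%. Alpha is taken as 0.05, as in the Abstract, and two-sided as an assumption. Statistical methods prints 0.05%, but taken literally that would need 104 per group.

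- Normal approximation: n per group = 2 × (1.960 + 0.842)² / 0.6² = 15.70 / 0.36 = 43.6, so 44, as in Statistical methods.
- The t-test version gives 44.6, so 45, as in the Abstract.
- With 10% attrition: 45 / (1 − 0.10) = 50, the recruitment target.

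The sample size reproduces. Nothing in it depends on the amount of usual care, so the point lies elsewhere.

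**The passages side by side.**

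- *What controls may use:* general practitioner, community or cancer-centre services, including mental health services.
- *What controls are told:* starting CBT or a new psychotropic outside the trial removes their data.
- *What is recorded at baseline:* psychotropic medication and whether psychological support is being accessed, in both arms.
- *What is recorded afterwards:* changes that participants choose to report. No scheduled question is stated.
- *What both arms already complete:* online questionnaires at the start, mid-point and end of the 16 weeks.

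Three things follow. Care during the 16 weeks is captured passively. The incentive to report differs by arm, because only one arm is told of a consequence. A scheduled way to ask already exists in both arms and is not stated to be used for this.

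**Illustration of size, all care inputs assumed.** Suppose 30% of controls would start effective care in ordinary practice but only 10% do so while waiting, and that such care is worth 0.3 to 0.5 SD.

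- Shift in control mean, low: (0.30 − 0.10) × 0.3 = 0.06 SD.
- Shift in control mean, high: (0.30 − 0.10) × 0.5 = 0.10 SD.
- As a share of the planned effect: 0.06 / 0.6 = 10%; 0.10 / 0.6 = 17%.

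The protocol gives no uptake figure for either arm. The range shows only what such a gap would be worth if it existed.

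**Omission of controls, fraction assumed.** With 50 in the iCBT arm, effect 0.6 and two-sided alpha 0.05 (t-test), power is 84% with 50 controls. It is 82% if 10% of controls are omitted (45 left), 80% if 20% are omitted (40 left) and 77% if 30% are omitted (35 left). The loss of numbers is minor. What matters is that removal depends on events after randomisation in one arm, and on who reports them.

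**The case against.** A reader might infer that the trial cannot test iCBT against usual care at all. The documents do not support this. Controls are expressly free to use their ordinary services, allocation is randomised, and the contrast of iCBT plus usual care with usual care while waiting is a valid one. Nor is the wait concealed: it is stated in the Abstract and in both sections on the TAU arm, so relabelling the arm would be largely a matter of wording.

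A reader might also infer that waiting suppresses care-seeking. That is plausible, but no passage gives care uptake or shows that waiting lowers it. The article states the later move to iCBT but does not show how it was put to participants.

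A third tempting inference is that care is demonstrably recorded unevenly. The iCBT arm does have more contact: individual emails after Lessons 1 and 2, and this invitation: "Participants will have the opportunity to volunteer feedback about their most recent lesson/week(s) before each subsequent lesson". But that feedback concerns the lessons and is not described as a route for reporting outside care. Control questionnaires are reviewed too, with clinician contact for unexpectedly high scores or significant change, and the request to report changes covers all participants. Uneven recording is a risk, not a documented fact.

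Finally, outside care is not wholly unmeasured. There is a baseline record and a reporting route. Table 1 lists questionnaires only, and the fuller protocol, which is not shown, might schedule a form on concomitant care.

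These objections limit the point but do not remove it. The article states its mechanism for care after baseline, that mechanism is passive, and a disincentive to report is stated for one arm only.

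**Conclusion.** The point holds as one about description and interpretation. The randomised comparison stands, and its proper name is iCBT plus usual care against usual care while waiting for iCBT. As printed, the plan cannot reliably say how much usual care either arm received, because later care depends on self-initiated reports and controls have a stated reason to withhold them. No effect on the estimate can be derived from the documents; the 0.06 to 0.10 SD above rests wholly on assumed uptake and benefit. The omission rule for controls and the intent-to-treat analysis cannot both stand as written and must be reconciled. The change is worth making because it is cheap, not because the result would otherwise be invalid. This rests on the article's text; if the full protocol schedules questions on outside care in both arms, the measurement part of the point falls away.

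**What to change.** Add two fixed items to the existing mid-point and post-treatment questionnaires in both arms: current psychotropic medication, and any psychological support since the last questionnaire. Tabulate care received by arm beside the primary result. State the conclusion as iCBT plus usual care against usual care while waiting for iCBT.

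Use the items to describe care, not to remove participants from the intent-to-treat analysis. Reconcile the omission rule in the consent paragraph with the intent-to-treat statement in Statistical methods; while the rule stands, the new items would carry the same disincentive to answer frankly.

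The cost is two questions on forms already scheduled, one table and some wording. The form becomes slightly longer. The first patient was enrolled on 1 March 2016, so the items will be missing for anyone already past those time points, and the table should report how many participants answered them in each arm.
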